### Outcome assessments

The intervention group and the control group will receive identical outcome assessments at two evaluation contacts. All participants will receive a questionnaire regarding motivation for changing physical activity behaviour two weeks after the health check and will be invited for fitness testing and asked to fill out a questionnaire after one year (Figure 1).

### Primary outcome

#### Fitness level

The criterion measure of fitness is maximal oxygen uptake, which can be expressed in relative (mL O_2_/min/kg) or absolute (L O_2_/min) terms [23]. Fitness level will be assessed as both a continuous and a categorical outcome. Specifically, mean levels of absolute and relative fitness will be assessed, and participants will be categorized according to their relative fitness level into five fitness groups (low, fair, average, good, high) based on pre-specified cut-offs [21]. The prevalence of low fitness is the specific categorical outcome of interest.

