**Methods/Design:**

An open-label, household-cluster, randomized controlled trial with a two-group parallel design is used. The trial is embedded in a population-based health promotion program, “*Check your Health Preventive Program*”, in which all 30–49 year-old citizens in a Danish municipality are offered a preventive health check. In each arm of the trial, 750 citizens will be recruited (1,500 in total). The primary outcome is cardiorespiratory fitness level assessed by submaximal cycle ergometer testing after one year. An intermediate outcome is the percentage of participants increasing motivation for physical activity behaviour change between baseline and two-weeks follow-up assessed using the Transtheoretical Model´s stages of change. Secondary outcomes include changes from baseline to one-year follow-up in physical inactivity prevalence measured by a modified version of the questions developed by Saltin and Grimby, and in self-rated health measures using the Short-Form 12, Health Survey, version 2.

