### Sample size

The sample size is estimated to be 1,500 participants in total. This sample size allows for a categorical analysis of fitness level and is calculated on the basis of the following assumptions: 1:1 randomization, false positive error rate of 0.05, power of 0.8, intracluster correlation coefficient of 0.05 and categorical analysis with a power to detect a difference of 10% in the prevalence of very low fitness between the study groups. We determined this 10% difference to be clinically meaningful based on expert opinions and criteria employed in other research [26]. The intracluster correlation coefficient was included to reflect a possible clustering effect of the GPs (n =46), which is seldom greater than 0.05 in primary care settings [27]. The estimated sample size accounts for a 30% loss to follow-up.

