### Statistical methods

Statistical analysis will be performed using STATA 12.0 software. Continuous variables are presented as mean ± standard deviation and categorical variables as absolute numbers and relative (%) frequencies. In the comparative analyses Student´s t-test will be used, when comparing means or changes in means of continuous variables and Chi^2^-test or Fisher’s exact t-test, when comparing proportions for categorical variables. Analyses will be adjusted for baseline physical activity. Stratified analyses will be performed on sex and age groups and analysis of motivation will be performed on a subgroup comprising precontemplaters, contemplaters, and preparators at baseline. All analyses will follow the intention-to-treat principle [28]. If appropriate, multiple imputation methods will be applied [29] (using data from social and medical national registries coupled with health check data), and sensitivity analyses will be performed. Moreover, the potential effect of clustering by the GPs will be investigated. The statistical significance level is set at p <0.05.

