### Evaluation choices

Every improvement of fitness is important for health and longevity [31–33]. However, the greatest gain results from improving fitness at the low end of the fitness-range [34]. On this basis, we chose to evaluate the effect of fitness testing on both mean level of fitness and the prevalence of very low fitness in the primary analysis. Longitudinal studies have shown that only 50% of participants follow-through on positive intentions to change physical activity behaviour [35]. Moreover, a majority of those succeeding may relapse to a less active or inactive status during the one-year follow-up period [36]. Thus, to acquire information about fitness testing as a motivational facilitator in preventive health checks, the stages of change was integrated as part of the evaluation. Adjacent stages have been successfully distinguished by intention to participate in strenuous, moderate, and mild exercise for adults [17, 37]. Engaging in regular moderate physical activity is shown to be sufficient to provide fitness improvements [38]. Hence, from the view that becoming moderately physical active is more achievable than becoming strenuously physical active, we chose a definition of regular moderate physical activity to stage participants. However, significant differences have been found only among the early stages and not between action and maintenance [17]. The analysis of this outcome will therefore be performed only on a subgroup.

In the secondary analyses, change in the prevalence of physical inactivity was included due to the existing evidence of a beneficial health effect of physical activity, independently of fitness [39], especially among the least active [40]. To broaden the perspective on the value of fitness testing, changes in general-, physical-, and mental self-rated health scores was included as well. Self-rated health is a subjective construct reflecting the individual´s integrated perception of health, and an association with mortality is well-established [41]. There have been some disagreements regarding the method for constructing the physical- and mental summary scores [42]. However, similar results have been demonstrated across different scoring algorithms [42].

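### Two or three versions of fitness sit in the primary analysis, each at an unadjusted 5% level and with no ranking or decision rule, while the trial is sized on only one of them

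*Protocol article*

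**What the plan says.** The abstract names one construct without a metric: "The primary outcome is cardiorespiratory fitness level assessed by submaximal cycle ergometer testing after one year".

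The Primary outcome section (Fitness level) splits it: "Fitness level will be assessed as both a continuous and a categorical outcome". On the continuous side, "mean levels of absolute and relative fitness will be assessed". On the categorical side, participants are placed in five groups by relative fitness (low, fair, average, good, high), and "The prevalence of low fitness is the specific categorical outcome of interest".

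Evaluation choices, in the Discussion, explains that the authors chose to evaluate "both mean level of fitness and the prevalence of very low fitness in the primary analysis". So more than one version is primary by intent.

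Statistical methods assigns t-tests to means and Chi-squared or Fisher tests to proportions, and closes with a single threshold: "The statistical significance level is set at p <0.05".

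The Sample size section assumes "1:1 randomization, false positive error rate of 0.05, power of 0.8, intracluster correlation coefficient of 0.05" and a 10% difference in the prevalence of *very low* fitness. It mentions no continuous version.

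**The concern.** A trial with several primary tests needs either one decisive test or a rule for combining them. The article gives neither. A significant result on mean relative fitness, on mean absolute fitness or on prevalence could each be reported as a positive primary finding, although the 5% error rate in the sample size belongs to the prevalence test only.

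The versions can also disagree. Relative fitness is divided by body weight, and both arms may be referred to behavioural programmes for high body mass index or inactivity, so weight may change over the year. Relative fitness could then rise while absolute fitness stays put, or the mean could move without the low tail moving. This is hypothetical, but the article has no rule for the verdict if it happens.

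**Working it through.** **1. The plan's own figure.** The total of 1,500 cannot be reproduced uniquely, because base prevalence and cluster size are not given. It can be reached. Read the 10% difference as percentage points and take 25% vs 15%, two-sided 0.05, power 0.8: 250 per arm, 500 in total. With 46 practices and 1,050 completers (1,500 × 0.7), the design effect is 1 + (1,050/46 − 1) × 0.05 = 2.09. Then 500 × 2.09 / 0.7 gives 1,494 (unrounded design effect). Other combinations also come close: 20% vs 10% with cluster size 1,500/46 gives 1,468, and 30% vs 20% with 750/46 gives 1,483. The figure is not shown to be wrong. It carries one test at 0.05.

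**2. Independent reference.** Three tests at 0.05: 1 − 0.95³ = 14.3%. Two tests: 1 − 0.95² = 9.75%.

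**3. Allowing for correlation.** Inputs, all assumed:
- Two-sided tests (sidedness is not stated).
- Correlation ρ between absolute and relative fitness: 0.4 to 0.9.
- Prevalence p of low fitness: 10% to 50%.
- Relative fitness approximately normal, so its correlation with the low-fitness indicator has size r = φ(z_p)/√(p(1−p)). For p = 20% this is 0.280/0.40 = 0.70; it is 0.58 at p = 10% and 0.80 at p = 50%.
- Absolute fitness correlates ρ × r with the indicator.

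Simulating trivariate normal test statistics under no effect gives the chance of at least one p<0.05:

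| ρ | p | Three versions | Mean relative + prevalence |
|---|---|---|---|
| 0.4 | 10% | 12.9% | 8.8% |
| 0.4 | 50% | 11.9% | 7.8% |
| 0.7 | 20% | 11.4% | 8.3% |
| 0.9 | 10% | 10.6% | 8.8% |
| 0.9 | 50% | 9.5% | 7.8% |

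The range is 9.5-12.9% for three versions (1.9 to 2.6 times 5%) and 7.8-8.8% for two (about 1.6 to 1.8 times).

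**4. Cross-check.** Simulated participant data with 525 per arm, no effect and ρ about 0.7 gave 11.5-12.0% for three versions. Counting only results that favour fitness testing, the rate was 5.4-6.0% against a nominal 2.5%.

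**5. Remedies compared.** One named primary at 0.05 keeps the error at 5% and the sample at 1,500. Bonferroni over three (0.05/3 = 0.0167 each) multiplies the required sample by ((2.394 + 0.842)/(1.960 + 0.842))² = 1.33, about 2,000 participants. Holding 1,500 instead drops power for 25% vs 15% (design effect 2.09) from 80% to about 66%.

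**The case against.** **No rule says that one hit is enough.** This stands. A reader might infer that the trial's primary false-positive rate simply is twice the stated 5%. The article does not support that: the inflation appears only if any one significant version counts as success, and if all had to be significant there would be none. The prevalence test taken alone keeps its 5%. What the article shows is a missing decision rule.

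**The count of three is open.** This also stands. Evaluation choices names only mean level and prevalence, which supports the two-version figure. The Primary outcome section lists both means, which supports three.

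**Test order and alpha allocation usually belong in the analysis plan, which is not shown.** True, and their absence from an article would not be a point on its own. But the article positively places several versions in the primary analysis under one threshold. A later plan that chose one would alter that published statement.

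**The sample-size endpoint is primary by implication.** Evaluation choices says otherwise by placing mean level beside it.

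**Motivation shares the first aim, so the family might seem larger still.** The article does not support this: it labels motivation an intermediate outcome, assessed at two weeks. It does not belong in the primary family.

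**A mean may be the better endpoint.** Strengths and limitations says the test is valid at group level but may misclassify individuals. This is a fair argument about which version to choose, not against choosing one.

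**Conclusion.** The point holds in conditional form. The article puts two or three versions of fitness in the primary analysis, each at an unadjusted p<0.05, without ranking or decision rule, and sizes the trial at 5% on prevalence alone. If any one significant version is taken as a positive primary result, the false-positive chance is about 8-9% (two versions) or about 10-13% (three). Those ranges rest on two-sided tests and on assumed correlations and prevalences. They leave out any further effect of ignoring clustering by household or practice.

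**What to change.** Name the prevalence endpoint used for the sample size, at one year, as the single primary outcome tested at 0.05, and state that the trial's verdict rests on it.

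First reconcile the wording: the Primary outcome section defines *low* fitness as one of five groups, while Sample size and Evaluation choices refer to *very low* fitness, which is not among the five. The powered category must be one of the defined groups.

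Then either test mean relative and, only if that is significant, mean absolute fitness in fixed sequence after a significant primary result, or label both means secondary.

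The cost is a short edit to the outcome, sample-size and analysis text, made before outcome data are seen. The sample size stays at 1,500 and the powered endpoint keeps its full alpha. The downside is that the two means can no longer carry a positive verdict on their own. If the sponsor prefers a mean as primary, the sample size would have to be justified for that mean.

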### Intermediate outcome

#### Motivation for physical activity behaviour change

Motivation for physical activity behaviour change will be operationalized by conceiving *intention* (to adopt a specific behavioural criterion) as a motivational construct. The Transtheoretical Model will compose the theoretical framework using the stages of change [17]. Stages of change conceptualize behaviour change as a progression through a series of five stages: *precontemplation* (*no intention* to engage in regular physical activity within the next six months), *contemplation* (*intention* to engage in regular physical activity *within the next six month*), *preparation (intention* to engage in regular physical activity *within the next 30 days), action* (regular physical activity behaviour initiated), and *maintenance* (regular physical activity has been performed for 6 month or more) [17, 24]. The three initial stages represent the motivational phase, in which intention is thought to increase [17]. We will consider progression from one of these three stages at baseline to a higher stage assessed two weeks after the health check as a motivational increase [17] and the percentage of participants increasing motivation as the specific outcome. Participants will stage themselves into one of the five stages according to their intention to engage in regular moderate physical activity defined as occurring on 5 or more days a week for at least 30 minutes (or 3 × 10 minutes) [23]. Moderate intensity is defined as producing increased heart rate, but being able to converse.

### Secondary outcomes

#### Physical inactivity

Leisure time physical activity level will be assessed using modified questions originally developed by Saltin & Grimby [16]. Participants will be asked to categorize their typical leisure time physical activity level as: ‘1. Mainly sedentary’ (e.g. reading, watching television or movies); ‘2. Low physical activity level’: engaging in light physical activities for more than four hours per week (e.g. leisurely walking, leisurely cycling, light do-it-yourself tasks, light house chores, table tennis, and bowling); ‘3. Moderate physical activity level’: engaging in sports or exercises minimum three times per week or vigorous leisure time activities (e.g. heavy gardening); or, ‘4. High physical activity level’: engaging in competitive sports or long distance running several times per week. Physical inactivity is defined as the lowest of the four activity categories (category 1). Change in reported physical inactivity prevalence from baseline to one-year follow-up composes the outcome.

### Self-rated health

Self-rated health will be assessed by the validated Danish version of the Short-Form-12 Health Survey, version 2 [18, 25]. It consists of 12 items covering 8 health domains of functioning and well-being, from which three self-rated health measures can be derived: a general health score, a physical component summary score, and a mental component summary score. All scores will be calculated by the standard scoring algorithm (U.S. derived) and presented as t-scores based on U.S. general population norms. The specific outcomes are changes in mean scores from baseline to one-year follow-up.

### Sample size

The sample size is estimated to be 1,500 participants in total. This sample size allows for a categorical analysis of fitness level and is calculated on the basis of the following assumptions: 1:1 randomization, false positive error rate of 0.05, power of 0.8, intracluster correlation coefficient of 0.05 and categorical analysis with a power to detect a difference of 10% in the prevalence of very low fitness between the study groups. We determined this 10% difference to be clinically meaningful based on expert opinions and criteria employed in other research [26]. The intracluster correlation coefficient was included to reflect a possible clustering effect of the GPs (n =46), which is seldom greater than 0.05 in primary care settings [27]. The estimated sample size accounts for a 30% loss to follow-up.

### Statistical methods

Statistical analysis will be performed using STATA 12.0 software. Continuous variables are presented as mean ± standard deviation and categorical variables as absolute numbers and relative (%) frequencies. In the comparative analyses Student´s t-test will be used, when comparing means or changes in means of continuous variables and Chi^2^-test or Fisher’s exact t-test, when comparing proportions for categorical variables. Analyses will be adjusted for baseline physical activity. Stratified analyses will be performed on sex and age groups and analysis of motivation will be performed on a subgroup comprising precontemplaters, contemplaters, and preparators at baseline. All analyses will follow the intention-to-treat principle [28]. If appropriate, multiple imputation methods will be applied [29] (using data from social and medical national registries coupled with health check data), and sensitivity analyses will be performed. Moreover, the potential effect of clustering by the GPs will be investigated. The statistical significance level is set at p <0.05.

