### Control group

As part of the CHPP, the control group will answer the same questionnaire as the intervention group and receive an identical preventive health check *without* fitness testing (Figure 1). Subsequent follow-up procedures are equal to those described for the intervention group.

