### Randomization and implementation

Randomization is handled by a data-manager with no scientific involvement. The eligible population for this trial was defined by the CHPP randomization, which was performed on clusters defined by households based on addresses obtained from the Danish Civil Register [6]. Using the same index individual per household, citizens randomized to group three in the CHPP will be further randomized by household to either intervention or control in the present trial (Figure 1). In practice, every second week will be scheduled for intervention group participants and the remaining weeks for control group participants. Group assignment will be maintained regardless of changes in the initially assigned appointment. Implementation and management of the booking-system is handled by a data-manager. The intervention, the outcomes, group assignment, and the future outcome assessments in this trial are unrevealed in the invitation for the CHPP. The health behavioural courses and the health consultations will be carried out unblinded due to the real-life setting. At the one-year follow-up, the personnel assessing the outcomes will be independent and blinded to group allocation.

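### SF-12 change is not adjusted for its own baseline, and the named t-test and Chi² tests cannot carry the promised adjustment: a loss of precision and consistency, not of validity

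*Protocol article*

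**What the plan says.** All references are to the Protocol article.

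- **Tests (Statistical methods).** For continuous variables, Student's "t-test will be used, when comparing means or changes in means of continuous variables". Chi² or Fisher's test is named "when comparing proportions for categorical variables".
- **Adjustment (Statistical methods).** "Analyses will be adjusted for baseline physical activity". No regression or stratified method is named for this, and no other covariate is given.
- **SF-12 (Self-rated health).** "The specific outcomes are changes in mean scores from baseline to one-year follow-up".
- **Inactivity (Physical inactivity).** "Change in reported physical inactivity prevalence from baseline to one-year follow-up composes the outcome". Inactivity is the lowest of the four categories of the leisure-time activity question.
- **Baseline data (Questionnaire; Control group).** Physical activity and self-rated health are both asked before the health check, and "the control group will answer the same questionnaire as the intervention group". Controls have no baseline fitness test.
- **Unit of randomisation (Randomization and implementation).** Citizens "will be further randomized by household to either intervention or control in the present trial".

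**The concern.** Three things do not fit together well.

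1. The SF-12 score is measured at baseline in both arms, but the planned comparison uses it only by subtraction. Subtraction fixes the weight of the baseline score at one, whatever its actual correlation with the one-year score. When that correlation is below one, the comparison is noisier than it need be, and a chance difference between arms at baseline carries into the result.
2. A two-sample t-test and a Chi² or Fisher test on a 2×2 table have no covariate term. The promised adjustment therefore needs another method, and the text does not say whether the adjusted or the simple result leads.
3. A change in prevalence is a difference between two correlated proportions within each arm, then compared between arms. A test of one proportion per arm answers a different question.

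At stake are some precision on the SF-12 scores, the match between outcome definition and test for inactivity, and clarity about which result leads.

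**Working it through.** **Inputs**

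- The Sample size section says "The sample size is estimated to be 1,500 participants in total", or 750 per arm. It allows for 30% loss: 750 × 0.70 = 525 per arm.
- Significance level 0.05 and power 0.80, from the same section. The section does not say one- or two-sided; two-sided is assumed, so z = 1.960 + 0.842 = 2.802.
- The correlation r between baseline and one-year SF-12 is **not in the documents**. The assumed range is 0.5 to 0.7, with 0.3 shown as a low case.
- Equal standard deviation (SD) at both times and independent participants are assumed.

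The article gives no figure for this point, so there is none to reproduce. The 1,500 enters only as a source of the 525.

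**Step 1: SF-12 precision.** Per participant, in units of SD²:

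- change score: 2(1 − r)
- one-year score adjusted for baseline: 1 − r²
- ratio, adjusted to change: (1 − r²) / [2(1 − r)] = (1 + r)/2
- smallest detectable difference: 2.802 × √(2 × variance / 525)

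| r | Change | Adjusted | Ratio | Detectable, change (SD) | Detectable, adjusted (SD) | 525 on change scores is worth, adjusted |
|---|---|---|---|---|---|---|
| 0.3 | 1.40 | 0.91 | 0.65 | 0.205 | 0.165 | 341 |
| 0.5 | 1.00 | 0.75 | 0.75 | 0.173 | 0.150 | 394 |
| 0.6 | 0.80 | 0.64 | 0.80 | 0.155 | 0.138 | 420 |
| 0.7 | 0.60 | 0.51 | 0.85 | 0.134 | 0.123 | 446 |

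For r of 0.5 to 0.7 the variance falls by 25% to 15%. In participants this is 1/0.75 = 1.33 to 1/0.85 = 1.18, as if 33% to 18% more people had been followed.

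**Step 2: chance imbalance.** If the arms differ by d at baseline, the expected shift in the change comparison is −(1 − r)d, which is 0.5d at r = 0.5 and 0.3d at r = 0.7 in size. By chance alone d has a standard deviation of √(2/525) = 0.062 SD, so a typical shift is 0.019 to 0.031 SD. Adjusting for the baseline score removes it. The shift averages to zero over randomisations, so it is noise, not bias.

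**Step 3: tests against adjustment.** The t-test uses two means and their variances; the 2×2 test uses four counts. Neither has room for baseline physical activity. Read literally, the two sentences in Statistical methods cannot describe one and the same calculation.

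**Step 4: inactivity.** A simulation used 525 per arm, 4,000 runs, an assumed prevalence of 15%, an assumed 6-point effect (15% against 9% at one year), an assumed correlation of 0.3 to 0.6 and no clustering.

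| Method | Power at r = 0.3 / 0.5 / 0.6 |
|---|---|
| Comparison of one-year prevalence | about 85% throughout |
| Comparison of the change in prevalence | 66% / 76% / 85% |
| Comparison adjusted for baseline | 87% / 91% / 94% |

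Type I error lay between 4.6% and 5.7% for all three methods. All are valid; they differ in what they estimate and in power.

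**The case against.** The strongest reply has four parts.

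- **A journal article condenses.** The model may be named in a fuller plan that is not shown, and simple comparisons followed by adjusted ones are an ordinary reading. This largely stands: much of the mismatch between tests and adjustment is an unnamed model. What remains is that the article pairs specific tests with an adjustment they cannot make and does not say which result leads. A reader might infer that the plan sets two rival analyses side by side; the text does not show that, since it can also mean that every analysis is adjusted.
- **Change scores are legitimate.** This stands. A reader might infer that the SF-12 comparison is biased or invalid. It is not: under randomisation it is unbiased with correct type I error, and the outcome definition and the t-test agree with each other.
- **Chi² can serve for inactivity.** A reader might infer that no Chi² test can address change or that the inactivity result would be unsound. The documents do not support this. They do not say that one-year prevalence alone will be tested. That comparison would be valid and, in the simulation, no less powerful than a test of change. A Chi² test on individual transitions could address change, though none is named. Moreover, the Questionnaire and Physical inactivity sections cite the same activity instrument, so adjusting for baseline physical activity would already adjust inactivity for its own baseline.
- **The SF-12 gain is an efficiency preference on a secondary outcome.** This is true, and the correlation is assumed. The 15% to 25% is also measured against an unadjusted change score; the gain over a change score adjusted for physical activity cannot be computed from the article. But the baseline scores are in hand in both arms, so the gain costs nothing.

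**Conclusion.** The point holds as one of precision and consistency. The SF-12 comparison leaves its own baseline out of the stated adjustment. For an assumed correlation of 0.5 to 0.7, including it would lower the variance by 25% to 15% against an unadjusted change score; the smallest detectable difference falls from 0.173 to 0.150 SD at r = 0.5 and from 0.134 to 0.123 SD at r = 0.7. These figures assume equal variances, 525 per arm and no clustering.

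The named tests cannot deliver the promised adjustment, and a Chi² test on one-year prevalence would not test the inactivity outcome as defined.

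Nothing here makes a planned comparison invalid. A reader might take the 18% to 33% equivalent in participants as a gain for the trial as a whole. It is not: the sample size rests on the prevalence of very low fitness, so no stated power figure changes. Nor could the primary outcome be adjusted for its own baseline, because controls have no baseline fitness test.

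**What to change.** State that the adjusted regression is the main analysis for each outcome and that the t-test, Chi² and Fisher comparisons are supportive.

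- **SF-12:** a linear model of the one-year score on arm, baseline score and baseline physical activity. The defined outcome can stay: using the change as the response with the same covariates gives the same arm effect.
- **Inactivity:** a binomial or logistic model of one-year inactivity on arm and baseline activity category, reported as a risk difference. Reword the outcome as inactivity at one year adjusted for baseline, so that definition and analysis agree.
- **Fitness:** a linear model for mean fitness and a binomial model for low fitness, on arm and baseline physical activity, with a risk difference for low fitness to match the 10% difference used in planning.
- **All outcomes:** standard errors that allow for households, the unit of randomisation. The Statistical methods section mentions clustering by general practitioner only.

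The cost is a change of wording before the data are analysed. Baseline SF-12 and physical activity are already collected in both arms; no extra visits, measurements or participants are needed.

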### Questionnaire

Prior to the health check, a web-based questionnaire regarding physical activity level [16], motivation for changing physical activity behaviour [17], self-rated health [18], smoking habits [19] and alcohol risk behaviour [20] will be answered. Participants have the opportunity to answer the questionnaire at the RHC, if support is needed.

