### Fitness testing

Fitness level will be assessed using a modified version of the Astrand submaximal cycle ergometer test [21] (Monark 939 E Pendulum Ergometer, Monark Exercise AB, Sweden) with a workload of 75 watt for women and 100 watt for men. Pedalling frequency is set between 60–70 rounds per minute. Heart rate will be measured continuously (polar T31 coded transmitter, Polar, Denmark) and recorded at 5.5 minutes, if participants achieve a steady-state pulse within a target interval of 120–170 beats/min. Steady state is defined as two consecutive heart rate recordings within 5 beats of each other [22]. If the target interval is not reached after 2 minutes of cycling, the workload will be increased with 35 and 50 watt for women and men, respectively. The test will proceed until a steady-state is reached. Fitness level will be estimated from the recorded heart rate and workload standardized to age and sex [21] (Monark 939 E Analysis Software, Version 3.0.9, Monark Exercise AB, Sweden). Blood pressure above 180/110 mmHg is considered a contraindication for performing the test. Moreover, the use of pacemaker or beta-antagonists results in exclusion from fitness testing due to unreliable heart rate responses [23].

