### The health check

In addition to fitness testing, the health check will include assessment of body weight and height, waist circumference, systolic and diastolic blood pressure, biochemical measures (lipid profile, glycated haemoglobin (HbA1c)), and lung function. Moreover, cardiovascular disease a risk score is calculated. The health check, including all measurements, is described in detail elsewhere [6].

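### The primary fitness comparison is adjusted only for self-reported activity, although sex, age, weight and height are available in both arms; this costs precision for mean fitness, not validity

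*Protocol article*

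**What the plan says.** The Statistical methods section sets the comparison in three sentences. For means: "In the comparative analyses Student´s t-test will be used, when comparing means or changes in means of continuous variables", with a Chi² or Fisher test for proportions. For covariates: "Analyses will be adjusted for baseline physical activity". For sex and age: "Stratified analyses will be performed on sex and age groups". No other covariate is named for the primary comparison.

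The baseline data are described elsewhere in the article:

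- Activity is self-reported: "Prior to the health check, a web-based questionnaire regarding physical activity level" and other items. The item has four categories (Physical inactivity).
- Body size is measured: "the health check will include assessment of body weight and height, waist circumference".
- Controls answer the same questionnaire and "receive an identical preventive health check *without* fitness testing".
- On the outcome itself, the Fitness testing section says: "Fitness level will be estimated from the recorded heart rate and workload standardized to age and sex".

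The Primary outcome section expresses fitness in L/min and in mL/min/kg, as means and as the prevalence of low fitness.

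**The concern.** The best covariate for a continuous outcome is usually its own baseline value. Controls do not have one here, by design, so the other baseline predictors matter more than usual. The plan takes one of them, a coarse self-report, and leaves out variables tied to the outcome by its construction: age and sex through the estimate, weight through the per-kg divisor.

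Stratified results by sex and age do not change the main comparison. Between-person variation that these variables could explain stays in its error term. At stake is the width of the confidence interval for mean absolute and relative fitness and, to a lesser degree, for the low-fitness prevalence.

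**Working it through.** **Inputs from the article.** 750 per arm; 30% loss; alpha 0.05 (two-sided assumed, as the article does not say); power 0.80; ICC 0.05; 46 GPs; a 10-point difference in prevalence of very low fitness. Evaluable per arm: 750 × 0.70 = 525. The article gives no SD, no R², no control prevalence and no cluster size.

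**The plan's own figure.** N = 1,500 cannot be reproduced uniquely, but it can be reached. For 25% against 15%, the pooled-variance formula without continuity correction gives 250 per arm. With 1,050/46 = 22.8 evaluable per GP, the design effect is 1 + 21.8 × 0.05 = 2.09. Then 250 × 2.09 / 0.70 is about 747 per arm, or 1,494 in total. For 20% against 10% with 32.6 per GP the total is 1,468; for 30% against 20% with 16.3 per GP it is 1,484. All lie within 3% of 1,500. None uses a covariate gain, so this point does not touch the sample size.

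**Mean fitness.** Let R² be the share of variance explained by sex, age and body size beyond activity, and let SD be the standard deviation left after adjusting for activity. Then

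detectable difference = (1.960 + 0.842) × √(2/525) × √(1 − R²) = 0.173 × √(1 − R²) SD.

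The equivalent sample multiplier is 1/(1 − R²). With the design effect of 2.09, each difference is multiplied by √2.09 = 1.446, and the relative gain is unchanged.

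| Extra R² (assumed) | √(1 − R²) | Detectable difference, no design effect (SD) | With design effect 2.09 (SD) | Power at the R² = 0 difference | Sample multiplier |
|---|---|---|---|---|---|
| 0 | 1.000 | 0.173 | 0.250 | 80% | 1.00 |
| 0.10 | 0.949 | 0.164 | 0.237 | 84% | 1.11 |
| 0.20 | 0.894 | 0.155 | 0.224 | 88% | 1.25 |
| 0.30 | 0.837 | 0.145 | 0.209 | 92% | 1.43 |
| 0.50 | 0.707 | 0.122 | 0.177 | 98% | 2.00 |

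To give R² a meaning: with equal numbers of men and women, a sex gap of d within-sex SDs gives R² = (d²/4)/(1 + d²/4) for sex alone. That is 0.12 at d = 0.75, 0.20 at d = 1 and 0.50 at d = 2. The article does not say which applies.

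**Low-fitness prevalence.** With a latent normal fitness variable, the variance reduction on the risk-difference scale is Var(E[Y|X]) / (p(1 − p)). For prevalences of 15% to 40% it is:

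- about 5–6% at latent R² 0.10
- about 9–13% at 0.20
- about 15–19% at 0.30
- about 28–33% at 0.50

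At R² 0.30 the standard error falls by 1 − √0.85 = 8% to 1 − √0.81 = 10%, against 16% for a mean. If the category cut-offs are age- and sex-specific, age and sex add almost nothing here, and what gain there is comes from body size.

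**The case against.** The strongest reply is that this is a preference about efficiency. A randomised comparison is valid with or without further covariates, and a full analysis plan, not shown, could list more. The chosen covariate has a rationale, since the Background calls physical activity the primary determinant of fitness. The sample size rests on prevalence, where the gain is smallest, and assumes no covariate gain. Imputation, if used, is already to draw on health check data.

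Much of this stands. The article contains no wrong figure here, and the stated power does not depend on the change. But the article does more than leave the covariates open: it names one. Mean fitness is also part of the primary analysis (Primary outcome, Evaluation choices). Neither the strata nor the imputation sentence brings sex, age or body size into the main comparison.

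A reader might infer that a chance imbalance in sex or weight would pass as a treatment effect. The article does not support that. Such imbalance is already reflected in the unadjusted standard error and the 5% error rate. With 525 per arm and half of them women (an assumption), the between-arm difference in the proportion of women has a standard deviation of √(2 × 0.25/525), about 3 percentage points. Adjustment would remove that noise; leaving it in creates no bias.

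**Conclusion.** The point holds as a loss of efficiency that can be avoided at no cost. It shows no bias and no error in the sample size. For mean fitness, the detectable difference could be 5% to 29% smaller if the omitted variables explain an extra 10% to 50% of the variance. That range is an assumption. The link with the outcome is plain from its construction, but its strength is not: the article reports no correlation, and its statement that the estimate is standardised to age and sex leaves open how much age and sex variation remains. A reader might take the upper rows of the table, equivalent to 43% to 100% more participants, as the established loss; nothing in the article fixes R² that high. For low-fitness prevalence the gain is modest, and how much of it age and sex can provide depends on cut-offs that the article does not reproduce.

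**What to change.** In Statistical methods, replace the adjustment sentence with a prespecified set: sex, age as a continuous variable, baseline weight and height (or BMI), and baseline physical activity. Use it in a linear regression for mean absolute and mean relative fitness, and in a model that yields a standardised risk difference for low fitness. Naming these models is needed in any case, because the t-, Chi² and Fisher tests take no covariates. Put the same covariates in any imputation model, and keep the sex and age strata as subgroup analyses.

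The cost is a sentence or two. Both arms already have these values, so nothing new is collected. The set should be fixed before outcome data are seen, since covariates added later would look post hoc.
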